### 2.7. Data Analyses

Interviews (Research Question 1)

Qualitative data will be analysed using qualitative content analysis, following the six steps outlined in Kuckartz’s method [39]. In the first step, audio recordings will be anonymised, transcribed verbatim by a member of the research team, and prepared for data analysis. Secondly, the main categories corresponding to the interview questions will be formed. In step three, codes will be generated within these main categories. In the next step, text passages of the main categories will be formed into subcategories. In step five, a category-based analysis will be conducted and reported in the final step. Throughout this process, a member of the research team will act as a critical friend, and challenge the author’s beliefs and offer feedback. Subsequently, themes will be deductively coded into the CFIR by the authors and again discussed with the critical friend. MAXQDA24 will be used for qualitative data analysis. Immediately after each interview, a team of researchers will deliberate on significant issues raised in the interview such as technical issues or problems with the workflow, and subsequently report these in writing to the study coordinator, where they are evaluated and discussed. Whenever feasible and necessary, adjustments are implemented promptly to enhance the overall quality of the intervention.

If participants decide not to take part in the second interview, their first interview will remain part of the analysis, unless they explicitly request deletion of their data, in which case all related material will be removed in accordance with ethical guidelines. All cases of attrition between the two interview rounds will be documented, and where possible, reasons for non-participation will be recorded. Thematic findings from both time points will be compared, with missing follow-up data considered in the interpretation of results.

To ensure culturally sensitive interpretation, the analysis will be conducted with cultural sensitivity, considering potential differences between German- and Turkish-speaking participants and discussing cultural nuances within the multilingual research team. Turkish-speaking coaches and neighbourhood mothers will contribute contextual insights to identify possible participation barriers and inform further adaptation of the intervention.

Implementation Quality Index (Research Question 2)

For the quantitative data analysis, all indicator values are aggregated at the family level and converted into a percentage value following the procedure outlined by Dowling and Barry [38]. This allows the individual indicator values within a dimension to be merged into an overall value between 0 and 1 for the respective dimension. The four overall ratings of the dimensions (dosage, adherence, quality of delivery, and responsiveness) are subsequently combined to yield a mean value for the overall quality of implementation.$$\begin{array}{c} Total\;Implementation\;Quality\\ =\frac{\left(Total\;Dosage+Total\;Adherence+Total\;Quality\;of\;Delivery+Total\;Participant\;Responsiveness\right)}{4} \end{array}$$

The items and indicators are not weighted, ensuring that all dimensions contribute equally to the quality of implementation. The visual binning method [40] is utilised to divide the overall assessment into four distinct categories, which are defined by the mean value and ±1 standard deviation: low implementation quality, moderately low implementation quality, moderate high implementation quality, and high implementation quality. Consequently, the families are allocated to the corresponding level of implementation quality. 

Missing data will be handled using an Available Case Analysis (ACA) approach, assuming data are Missing Completely at Random (MCAR). In line with Dowling and Barry [38], cases with more than 25% missing data in key variables will be excluded from the analysis to avoid bias and maintain the reliability of results.

Impact of Implementation Quality on fruehstArt effectiveness (Research Question 3)

Mixed models for repeated measures will be used to analyse the relationship between the Implementation Quality and the primary (BMI-SDS) and secondary outcomes (see [28]) of the effectiveness analysis (summative evaluation).

The intervention model shown in Figure 3 illustrates the relationships to be analysed and is divided into three main areas: Input, Process, and Outcomes. The ‘Input’ includes the previously described key components of the intervention, designed to work synergistically to support participants. The influence of implementation quality and other contextual factors will be analysed at the ‘process’ level as part of the formative evaluation. Certain variables within the implementation may act as mediators between the inputs and the outcomes (primary and secondary). The intervention model aims to capture the complex interactions between various implementation and contextual variables and their effects on the primary and secondary and serves as basis for modelling further statistical analysis.

## 3. Discussion

The results of the formative evaluation are expected to sustainably improve the quality of future implementation of fruehstArt through adapting the intervention’s structure and modifying the implementation concept. This will bridge the gap between current evidence and practical application in healthcare as there is a disconnect between what research shows to be effective and what is actually implemented in clinical and organisational settings [41].

By uncovering the factors that contribute to implementation quality and examining the relationship between implementation quality and intervention outcomes, this study will enhance our understanding of the key determinants of successful intervention implementation based on multi-level data collection from service providers and participating families. It will also elucidate how these determinants are associated with the effectiveness of the intervention.

Strengths

One of the strengths of this formative evaluation at process level is its mixed-methods design, which includes both qualitative and quantitative data from participating families and service providers (coaches and paediatricians). Evaluating an intervention from multiple perspectives allows a comprehensive understanding of the needs and preferences of families with overweight or obese children, as well as those of service providers. This helps to investigate whether the intervention was implemented accordingly to those needs and wishes of the target groups to increase its appeal and applicability. In addition, the provision of ongoing, interactive feedback facilitates immediate modifications to the intervention to ensure that it remains effective and relevant to participants’ needs. This study will also identify factors that may influence the feasibility of fruehstArt, such as availability of resources, time constraints of families or cultural and personal preferences regarding lifestyle choices.

The development of an Implementation Quality Index based on existing evidence and experience is another strength of this study, as it provides a valuable basis for linking quantitative data on implementation quality with the primary and secondary outcomes of the effectiveness analysis (summative evaluation). Linking the data will allow exploration of the conditions under which the fruehstArt intervention achieves its intended effects. By linking the data, it will be possible to determine not only whether the fruehstArt intervention is effective, but also under what conditions of implementation it is effective. This area has been underexplored in previous research, so the index facilitates systematic comparisons and increases the robustness of study conclusions, thus filling a significant gap in the existing literature.

Findings and Implications

Findings from the formative evaluation will inform the adaptation and further development of the fruehstArt intervention before potential large-scale implementation. Insights will be shared with consortium partners and relevant stakeholders to enable refinement of the programme and to derive implementation strategies, and policy recommendations for the prevention of childhood overweight and obesity in Germany.

Limitations

Evaluating processes in real time may miss longer-term challenges or successes that emerge after the evaluation period which can lead to bias and inaccuracy. Difficulties in recruiting participants may lead to a smaller sample size than anticipated, which could limit the validity of the results. Additionally, interviewing only a relatively small number of participating families and paediatricians may not adequately capture the diversity of experiences, perspectives, or contextual factors present across the full study sample and all service providers. Another major challenge is the management of missing data, which could introduce bias or reduce the statistical power of the analyses. However, missing data is being minimised through user-friendly data collection via an e-health platform and a regular reminder management.

Qualitative data also may introduce bias due to subjective interpretations by participants or researchers making it difficult to draw general conclusions about this study’s overall implementation process. The potential for selection bias also exists, as the families and paediatricians who participate might have a greater interest in the topic or better resources. Therefore, participating families and paediatricians might differ systematically from those who do not, potentially skewing the results.

Lastly, all indicators of the Implementation Quality Index were self-developed and therefore not psychometrically tested. This may limit the validity and reliability of the findings. To compensate for that, the development has undergone expert consultations also including communication with the authors who developed the original version of the index. Moreover, Adherence and Quality of Delivery were partly based on coach self-assessments, which may introduce bias. However, the inclusion of parental evaluations of coaching quality provides an additional external perspective, allowing us to validate and contextualise the coaches’ ratings.

In addition, all four dimensions of the Implementation Quality Index were weighted equally. While this approach follows the procedure proposed by Dowling and Barry [38] and allows for comparability, it may not fully capture potential differences in the relative importance of each dimension for implementation success. For this reason, the evidence base will be continuously monitored throughout the project so that adjustments can be made to the weighting of individual dimensions if necessary.

Conclusions and outlook

While this formative evaluation provides valuable insights into the implementation of fruehstArt, some limitations concerning the feasibility and generalisability of findings should be acknowledged. As implementation processes are highly context-dependent, the transferability of findings to other healthcare settings or populations should be interpreted with caution.

Moreover, the anticipated results have the potential to advance theoretical understanding of how contextual and behavioural factors influence implementation success in childhood obesity prevention. By applying and potentially refining constructs of the Consolidated Framework for Implementation Research (CFIR), this study may contribute to the ongoing development of theory-driven approaches to designing and evaluating preventive interventions in early childhood.

Finally, the results will also contribute to a stronger consideration of the connection between formative and summative evaluation. If, as assumed, a connection between implementation quality and effectiveness can be demonstrated, this would underpin the importance of implementation in the context of evidence-based intervention development and delivery.

If fruehstArt demonstrate effectiveness, it could serve as a model for broader implementation within the German healthcare system. A scaled-up version might support improvements in early prevention and intervention structures, thereby contributing to healthier developmental trajectories in early childhood.

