### 2.2. The Evaluation Design of FruehstArt

The evaluation concept of this study employs a mixed-methods approach, incorporating a summative evaluation, formative evaluations at process and system level, and a health economic analysis. The project is funded by the Joint Federal Committee for a period of 48 months, from 2022 to 2026. The intervention is currently being piloted in North-Rhine-Westphalia, the most populous federal state of Germany.

The summative evaluation is conducted as a randomised controlled trial (RCT) including 812 children. It assesses the effectiveness of fruehstArt by analysing changes in the primary outcome, BMI-SDS, at 12 months in the intervention group (IG) in comparison to the control group (CG). Children are recruited from paediatric practices and obesity centres participating in the project and randomised in a 2:1 (541:271) ratio. Measurements of weight and height are conducted quarterly in paediatric practices.

The IG receives all key components of fruehstArt for 12 months, while families in the CG receive a motivational interview conducted by a paediatrician every four months and the current standard of care. The CG also has limited access to the fruehstArt web application for completing study questionnaires.

Parents will complete questionnaires at three time points: baseline (T0), six months (T1), and 12 months (T2) after enrolment. These questionnaires will be used to collect comprehensive data on a variety of characteristics, including parental health literacy, the child’s daily lifestyle habits, the parents’ level of physical activity and the parents’ quality of life. In addition, a motor skills test (side-to-side jumping), conducted by coaches and study coordinators at baseline (T0) and after 12 months (T2), is included as part of the summative evaluation to assess potential changes in children’s physical competence in relation to physical activity and weight development [29].

A more detailed overview of the overall evaluation design of fruehstArt can be found in the study protocol of the overall study [28]. The methodology relevant to this formative evaluation will be described below.

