### 2.3. Objectives and Research Questions

The formative evaluation at the process level aims to identify barriers and facilitators of fruehstArt, the quality of the intervention, and the feasibility of implementation strategies. It also aims to describe and understand the contextual factors of the intervention to provide recommendations for adapting fruehstArt.

Based on the research objectives, the research questions that are addressed are as follows: What factors facilitate or hinder the implementation of the intervention components?What is the quality of implementation of fruehstArt and what differences can be observed between the families?Does implementation quality influence the effectiveness of the fruehstArt intervention?

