Potential interviewees will be contacted via email or postal letter and provided with study details. They can choose between in-person, online, or telephone interviews, which will last approximately one hour, be conducted by one researcher, and audio recorded with written consent.

Implementation Quality Index

Quantitative data to measure the Implementation Quality Index will be collected at T1 and T2 from both the coaches (n = 14) and all parents (n = 541) in the intervention group. No separate sample size estimation was conducted for the formative evaluation, as it builds on the intervention group of the summative evaluation, for which a sample size calculation was performed. Data will be used from the fruehstArt app that includes a questionnaire specifically tailored and developed for the purpose of the formative evaluation study.

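### The implementation index exists only in the intervention arm, so research question 3 can show an association with outcome but not the conditions under which fruehstArt is effective

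*Protocol article*

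**What the plan says.** Research question 3 (section 2.3) asks: "Does implementation quality influence the effectiveness of the fruehstArt intervention". Section 2.2 fixes what effectiveness means: the change in BMI-SDS at 12 months "in the intervention group (IG) in comparison to the control group (CG"), in a "randomised controlled trial (RCT) including 812 children", "randomised in a 2:1 (541:271) ratio".

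The index data are collected at T1 and T2 "from both the coaches (n = 14) and all parents (n = 541) in the intervention group" (section 2.5). The four dimensions (section 2.6 and Table 1) rate coaching sessions, rehabilitation used, app use, the relationship with the coach and the family's response. According to section 2.2, the control group receives motivational interviews and standard care, and has app access only for questionnaires.

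The one analysis stated for this question is in section 2.7: "Mixed models for repeated measures will be used to analyse the relationship between the Implementation Quality and the primary (BMI-SDS) and secondary outcomes". The same section describes an intervention model in which "Certain variables within the implementation may act as mediators between the inputs and the outcomes (primary and secondary"). The Strengths part of the Discussion then concludes that "it will be possible to determine not only whether the fruehstArt intervention is effective, but also under what conditions of implementation it is effective".

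**The concern.** Whether the programme works better when it is well implemented is a question about how the difference between arms changes with implementation quality. Answering it requires knowing how families who would implement well, and families who would implement poorly, fare without the programme. The index cannot supply this, because it is not defined for control families. What remains is a comparison of intervention families with one another, and they were not randomised to their level of quality.

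The article itself describes ways in which quality and prognosis can be linked, and they point in different directions:

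- Families with more interest or better resources may engage more and also do better anyway. The limitations recognise this for who takes part in the study, but not for who implements well within the intervention group.
- The number of coaching sessions follows family need, and rehabilitation is offered only above the 97th BMI percentile (section 2.1). Both count towards dosage, so heavier children may score higher on dosage.
- The index is also measured at T2, when the primary outcome is measured. A family whose child has done well may rate the coaching, or be rated by the coach, more favourably.

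At stake is the conclusion the study may draw. A within-arm association of this kind could be reported as showing when the programme works, although it could arise with no such effect, or hide a real one.

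**Working it through.** **Allocation.** 812 × 2/3 = 541.3 and 812 × 1/3 = 270.7, so the stated 541:271 reproduces. The total of 812 cannot be re-derived, because the article gives no alpha, power, effect size, SD or dropout. Children without an index value: 812 − 541 = 271.

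**How often confounding alone gives p<0.05.** Assume that quality has no effect and that one family trait C correlates a with the index and b with outcome. The index and outcome then correlate r = a × b. With n = 541, Z = arctanh(r) × √(541 − 3) = arctanh(r) × 23.19, and P(p<0.05) = Φ(Z − 1.96) + Φ(−Z − 1.96). The correlations are assumptions; the article gives none.

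| a | b | r | Z | P(p<0.05) |
|---|---|---|---|---|
| 0.2 | 0.2 | 0.04 | 0.93 | 15% |
| 0.3 | 0.3 | 0.09 | 2.09 | 55% |
| 0.4 | 0.3 | 0.12 | 2.80 | 80% |
| 0.5 | 0.3 | 0.15 | 3.51 | 94% |

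The calculation takes one time point, complete data and no covariate adjustment. It is two-sided, so the sign of the bias does not matter.

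**Check by simulation.** 1,000 trials of 541:271 per scenario, outcome SD about 1, standardised index seen in the intervention group only, and a linear regression in that group as a simple stand-in for the mixed model. With zero programme effect, the index coefficient was significant in 4.6% of trials without confounding, 55% (0.3 and −0.3), 93% (0.5 and −0.3) and 100% (0.5 and −0.5). This agrees with the formula.

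**Whether setting quality bands against the control group helps.** Section 2.7 cuts the index at the mean and ±1 SD. For a normal index, families above +1 SD have a mean index of φ(1)/(1 − Φ(1)) = 1.525. With correlations 0.5 and −0.5 and zero programme effect, the expected difference from control is 1.525 × (−0.25) = −0.38 SD for the top band and +0.38 SD for the bottom band. The simulation gave −0.38 and +0.38, with an overall arm difference of 0.00. The whole control group is the wrong comparator for a selected band.

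**Whether the data can separate the two explanations.** Take two truths:

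- (a) A uniform effect of −0.2 SD, no modification by quality, confounding 0.5 and −0.5. The mean outcome in the intervention group is −0.2 + (0.5 × −0.5) × index = −0.2 − 0.25 × index.
- (b) No confounding, an average effect of −0.2 SD, and a true modification of −0.25 SD per SD of quality. The mean is again −0.2 − 0.25 × index.

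| Simulated result | (a) | (b) |
|---|---|---|
| Index coefficient, intervention group | −0.248 | −0.249 |
| Arm difference | −0.196 | −0.198 |
| Top band versus control | −0.581 | −0.578 |
| Bottom band versus control | +0.180 | +0.181 |

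The planned comparisons look the same whether quality changes the effect or engaged families simply do better.

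**The case against.** The best defence has four parts.

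**Much of the wording is already associational.** Section 2.7 speaks of a relationship, the opening of the Discussion of determinants being associated with effectiveness, and the sentence just before the quoted one only of exploring conditions. This is true, and it shows that the authors know the weaker reading. But research question 3 and the quoted sentence go further, and the limitations do not mention non-randomised quality or the missing control contrast.

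**Model terms may be in documents not shown.** Section 2.7 does not expressly confine the analysis to the intervention group, and covariates may be set out in the overall study protocol or an analysis plan. So no covariate omission is alleged here, and the exclusion of controls is an inference from where the index exists. The point stands regardless: no control family has an index value, and the band-versus-control contrast shown above is confounded. Methods that use baseline covariates in both arms could attempt the question, but only under further assumptions that cannot be tested.

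**Quality is not only a family trait.** Adherence is rated by coaches and quality of delivery concerns the provider, so family self-selection is not the whole index. This also stands, and is one reason why neither the direction nor the size of bias can be fixed in advance.

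**Two stronger readings are tempting but unsupported.** A reader might infer that a mediation analysis is promised. Section 2.7 only says that variables may act as mediators, within a conceptual model; no mediation test is stated. A reader might also infer that scale-up depends on the index result. The closing section ties broader implementation to demonstrated effectiveness, which is the randomised comparison. The link between quality and effectiveness is put there as a conditional expectation, whose stated consequence is to underline the importance of implementation.

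**Conclusion.** The claim to determine under what conditions of implementation fruehstArt is effective is wrong as written, because the index has no counterpart in the control group. Whether the programme is effective is answered by the randomised comparison and is untouched by this point. What research question 3 can deliver is an association within 541 intervention families.

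The probability of a nominally significant result when quality has no effect runs from about 15% to about 80% across the two assumed pairs of correlations (0.2 and 0.2; 0.4 and 0.3). It stays near 5% without confounding and approaches 100% with strong confounding. These figures illustrate what is possible; they do not estimate the bias in this study. A reader might infer that the association must flatter the programme, but the documents do not support this, because dosage rises with need and BMI percentile and could push the association the other way.

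**What to change.** 1. State research question 3 as an exploratory association within the intervention group, adjusted for baseline BMI-SDS and the other prognostic baseline variables collected (for example age, sex, SES, language, parental health literacy and coaching strand).
2. In the Strengths part of the Discussion, replace the claim to determine conditions of effectiveness with associational wording, in line with the sentence before it.
3. Add to the limitations that implementation quality is not randomised, has no control-group counterpart, and is partly measured at the same time as the primary outcome.
4. State that the within-group relation will not be interpreted as effect modification or mediation.
5. Optional sensitivity analysis: predict quality from baseline variables in the intervention group with cross-fitting, assign the predicted score to all 812 children, and test arm × predicted quality on 12-month BMI-SDS. This restores a randomised contrast, but for a different estimand: effect modification by baseline-predicted quality, not by quality as delivered. It needs the predictors in both arms, which the article does not show for SES or migration background (named only as interview selection criteria), and it is less precise.

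Items 1 to 4 cost wording and a covariate list. Item 5 costs one further model. The article schedules the final data export for June 2026 with analysis afterwards, so all of this can be settled before analysis and without new data collection.
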